## Abstract

Soft Tissue Sarcomas (STSs) are rare malignant tumors characterized by a marked histological heterogeneity. Their standard of care is the surgical resection with adjuvant therapies, but these interventions induce sensorimotor impairments, pain, and a reduction quality of life. In this context, systematic evidence on its role in STS patients is currently lacking. This prospective, multicenter, observational study aims to evaluate the effects of a personalized rehabilitation protocol on clinical characteristics, motor performance, and quality of life in patients undergoing surgery for STS of the trunk and lower limbs. Patients will be recruited and assessed at four time-points: baseline (pre-surgery), post-surgery (within 7 days post-surgery), pre-rehabilitation (within 30 days post-surgery), and post-rehabilitation (within 90 days post-surgery). Rehabilitation will combine conventional physiotherapy with robotic technologies, delivered over two daily sessions for approximately 60 days. The assessments will include gait analysis, clinical scales, and patient-oriented questionnaires. The primary endpoint will be the improvement in functional status quantified in terms of Toronto Extremity Salvage Score differentiated for the Lower Limb, while secondary outcomes will include biomechanical parameters, pain, and quality of life. This trial will represent the first study quantifying the impact of rehabilitation in patients with STS, with the potential to generate novel prognostic factors and provide an evidence-based framework for future tailored rehabilitation protocols.

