### Study design and setting

2.2

The clinical investigation was designed as a prospective, observational, multicenter, uncontrolled study conducted on patients with STS localized in the trunk or in the lower limbs. It was approved by the Ethics Committee of the Fondazione Policlinico Universitario Campus Bio-Medico (Protocol number PAR 77.22 OSS), by the Ethics Committee Lazio 1 (Protocol number 420/CE Lazio 1) and registered on ClinicalTrials.gov (ID NCT06282237).

The study will be conducted at two centers: the Fondazione Policlinico Universitario Campus Bio-Medico as study sponsor, recruitment and surgery center, and the Centro Santa Maria della Provvidenza of the Fondazione Don Carlo Gnocchi in Rome as rehabilitation center.

The study is presented following the Standard Protocol Items: Recommendations for Interventional Trials (SPIRIT) Chan et al. (14) reported in **Figure 1**.

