
### Study intervention

2.7

Following recruitment for surgical treatment, a multidisciplinary team will define the optimal therapeutic approach taking into account patient-related factors (e.g., age, past medical history, and comorbidities) as well as tumor-specific characteristics (e.g., histology, size, and anatomical location). The team will also consider the eventual addition of radiotherapy and/or chemotherapy before or after the surgery as neoadjuvant or adjuvant therapies, respectively: the use of brachytherapy is not planned in the study. Subsequently, the patients will undergo STS radical resection to obtain negative margin classified as R0 in accordance with the guidelines of the Union for International Cancer Control Hermanek and Wittekind (23) and a reconstructive plastic surgery recovering the soft tissue defects.

Afterwards, at the rehabilitation center, all patients will undergo the same (i.e., no randomization) rehabilitation treatment consisting of postural steps, bed–wheelchair transfers, verticalization, ambulation without weight bearing on the operated limb or with partial bearing and ambulation with gradual weight bearing with or without aid Galluccio et al. (24).

The rehabilitative intervention will include two 50-minute sessions per day, six days per week for a total duration of approximately 60 days and it will imply both a robotic and conventional treatment.

As for the former, the recover of muscular strength, balance, proprioception and lower limb joints range of motion will be pursued using one or more of the following rehabilitative robots:

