#### Primary endpoint

2.10.1

The primary endpoint of the study will be the improvement of TESS-LL score between *T_0_*(baseline) and *T_3_*(end of the rehabilitation treatment).

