The results of this work are expected to generate insights into the STSs effects on human biomechanics, pain and QoL. Moreover, considering factors such as tumor location, surgical approaches and additional clinical variables, the study will have a huge prognostic factor foreseeing long-term functional outcomes. Such evidence could serve as a baseline for the design and development of highly personalized rehabilitation protocols, ultimately setting new standards in the management of patients with STS.

Finally, a unique strength of the present study will lie in its strong multidisciplinary team, bringing together general and plastic surgeons, physicians, physiotherapists and engineers. This collaborative framework not only will ensure methodological rigor and clinical relevance but also it will pave the way for translational impact, bridging the gap between technological innovation and patient-centered care.

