## Conclusion

4

This study aims to deeply evaluate and objectively quantify the effects of a personalized rehabilitation treatment following STSs surgical treatment on patients clinical characteristics, sensorimotor performance and QoL.

Up to a maximum of fifty patients will be recruited and assessed at four time-points: baseline, post-surgery, pre- and post-rehabilitation. The rehabilitation will combine conventional physiotherapy with robotic technologies and it will be delivered over two daily sessions for 60 days. The assessments will include gait analysis, clinical scales and patient-oriented questionnaires.

The expected results will hold significant implications. First, they will provide objective evidence on the short- and mid-term functional outcomes of STS surgery. Second, the study will support the development of personalized rehabilitation pathways identifying prognostic factors related to tumor location, surgical approaches and patient characteristics. Third, the adopted structured methodology and multidisciplinary approach will serve as a reproducible model for future trials in similar rare and complex diseases.

Nonetheless, the study will be affected by limitations. The study period will be limited to three months, restricting the possibility of retrieving long-term recovery. The adopted approach will prevent the evaluation of emerging modalities such as telerehabilitation, which could improve accessibility and continuity of care. Furthermore, the lack of nutritional and genetic assessments will limit the capacity to explore biological determinants of recovery.

Future investigations should therefore extend follow-up, integrated digital and remote rehabilitation solutions and consider both genetic and nutritional assessment.

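### The article promises to quantify the effect of rehabilitation and to foresee long-term outcomes, but an uncontrolled before-surgery to 90-day comparison supports neither, and the limitations omit the missing control

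*Protocol article*

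**What the plan says.** **Effect claims.** The Abstract says "This trial will represent the first study quantifying the impact of rehabilitation in patients with STS". The Conclusion (Section 4) says "This study aims to deeply evaluate and objectively quantify the effects of a personalized rehabilitation treatment", and the Introduction has an equivalent sentence. Section 2.1 makes the effects of rehabilitation the main purpose. Section 2.7 says the T3 visit serves to assess the impact of the rehabilitation treatment and of the study as a whole.

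**Design.** Section 2.2: "The clinical investigation was designed as a prospective, observational, multicenter, uncontrolled study". Section 2.7: "all patients will undergo the same (i.e., no randomization) rehabilitation treatment". Section 2.5 calls the results exploratory and takes 50 patients from the centre's annual caseload.

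**Primary contrast.** Section 2.10.1: "The primary endpoint of the study will be the improvement of TESS-LL score between" T0 and T3. By the Figure 1 caption, T0 falls within 7 days before surgery and T3 within 90 days after it. Section 2.12.1 tests this change with a paired non-parametric test and calls a patient a responder if the change exceeds 7 points.

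**Long-term claim and limitations.** The Discussion (Section 3) says "the study will have a huge prognostic factor foreseeing long-term functional outcomes". The Conclusion says "The study period will be limited to three months, restricting the possibility of retrieving long-term recovery". Its other stated limitations are that telerehabilitation is not evaluated and that nutritional and genetic assessments are lacking. It does not mention the lack of a control group.

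**The concern.** To quantify the effect of a treatment, the observed course must be compared with what would have happened without it. This design has no such comparison, and no planned analysis supplies one. The primary contrast adds a difficulty because it starts before the operation. Whatever surgery takes away, whatever returns by itself, and whatever radiotherapy or chemotherapy adds or removes are all inside the same number as rehabilitation.

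What is at stake is the conclusion the trial may draw. A significant improvement would be reported as a measured effect of rehabilitation. A net loss at T3 could be reported as failure even if rehabilitation helped. The article lists limitations but omits the one that bears on its headline claim.

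The long-term statement is a separate, smaller fault. No outcome is collected beyond about three months, so no long-term prediction can be fitted or checked.

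**Working it through.** **1. What the primary contrast contains.** For each patient,

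change(T0 to T3) = surgical loss + spontaneous recovery + effect of radiotherapy or chemotherapy, if given + effect of rehabilitation.

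Only the sum is observed. All patients have surgery and all receive rehabilitation, so the terms cannot be separated. Section 1 says these operations compromise lower-limb function, so the first term is expected to be negative.

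**2. The T2 to T3 contrast.** Section 2.12.2 compares gait at T2 with T3. Surgery is then in the past, but spontaneous recovery and any adjuvant therapy remain in the change. It measures change during rehabilitation, not the effect of rehabilitation.

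**3. Size, as an illustration.** The article gives no effect size, power or SD of change, so there is no figure of its own to reproduce. Inputs: n = 50 (Section 2.5); significance level 0.05 (Section 2.12.2), two-sided assumed; Wilcoxon signed-rank test (Section 2.12.1); SD of change 15, 20 or 25 points (assumed); normally distributed changes (assumed). Each setting was simulated 3000 times. Every change is a net change from the pre-surgical score.

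| Net mean change T0 to T3 | SD 15 | SD 20 | SD 25 |
|---|---|---|---|
| +7 | 89% significant | 67% | 47% |
| +10 | about 100% | 93% | 78% |
| −7 (worsening) | 89% | 66% | 47% |

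Check by normal approximation, power = Φ(|d| / (SD/√n) − 1.96), with d = 7:
- SD 15: 7 / (15/7.071) = 3.30, and Φ(1.34) = 0.91.
- SD 20: 7 / (20/7.071) = 2.475, and Φ(0.515) = 0.70.
- SD 25: 7 / (25/7.071) = 1.98, and Φ(0.02) = 0.51.

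These lie slightly above the simulated values, as expected for the rank test.

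The same row fits opposite truths:
- Rehabilitation effect 0 and all other causes +7 gives a net change of +7, a likely significant improvement at SD 15.
- Rehabilitation effect +7 and all other causes −14 gives −14 + 7 = −7, a likely significant worsening at SD 15.

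**4. The responder label.** If the mean net change is exactly zero, the share above 7 points is 1 − Φ(7/SD):
- SD 15: 1 − Φ(0.467) = 32%.
- SD 20: 1 − Φ(0.35) = 36%.
- SD 25: 1 − Φ(0.28) = 39%.

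A responder rate of this order therefore does not isolate rehabilitation either.

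**5. Long-term prediction.** The last visit is within 90 days of surgery (Figure 1 caption). The logistic models in Section 2.12.1 take responder status from the T0 to T3 change. They can therefore predict status at about three months and nothing later. The Discussion sentence goes beyond this and conflicts with the limitation that the Conclusion itself states.

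**The case against.** The strongest reply is that nothing is hidden. Section 2.2 says uncontrolled, Section 2.7 says there is no randomization, and Section 2.5 calls the results exploratory. In a rare disease a control arm may not be feasible, and the long-term sentence is one Discussion remark on which no endpoint or test depends. All of this stands as a description of the design. It does not limit the inference: the stated aim and conclusions remain causal. The exploratory label appears in the sample-size section, where it explains the choice of 50. No control arm is being requested.

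Four stronger readings are tempting, and the document does not support them:

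- A reader might infer that natural recovery alone would make the primary test significant. T0 is before surgery, so spontaneous recovery would first have to cancel the surgical loss and then add a net gain. The percentages above refer to that net gain.
- A reader might infer that T1 to T2 is an untreated run-in that could serve as a control. Section 2.7 places T2 before rehabilitation, but Section 2.9 has conventional physiotherapy running for the whole study period. Recovery may also slow by itself, so a difference in slope would not be a causal effect.
- A reader might infer that the intermediate visits go unused. Section 2.12.2 already compares the questionnaires by ANOVA or Friedman test, although not as a check on natural recovery.
- A reader might count the easing of weight-bearing limits as a rival explanation. Section 2.7 makes that progression part of the rehabilitation treatment.

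**Conclusion.** The point holds as a fault in what the article claims, not in what it collects. The primary contrast estimates net change over surgery, recovery, any adjuvant therapy and rehabilitation together. It cannot be read as the effect of rehabilitation in either direction. That follows from the design and needs no assumed number. The percentages show only how readily a net change from other causes would reach significance; they rest on assumed SDs and mean changes and do not forecast the result.

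The missing control should be among the limitations. The long-term claim conflicts with the 90-day horizon and with the Conclusion's own caveat. That caveat says long-term recovery is restricted, so it should not be read as ruling it out altogether; but with no later visit, the data offer no basis for the claim. The matter should be corrected because it determines what the trial may conclude.

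**What to change.** 1. In the Abstract, Introduction, Section 2.1, Section 2.7 (T3) and Conclusion, restate the aim as describing change over the surgical and rehabilitation pathway. Describe T2 to T3 as change during rehabilitation, not as its effect.
2. Add the absence of a control group to the limitations in Section 4. Say that surgical loss, spontaneous recovery and adjuvant therapy cannot be separated from rehabilitation.
3. In the Discussion, limit the prognostic statement to outcomes at about three months.
4. Optional, as context only: display TESS-LL change over T1 to T2 and T2 to T3 by actual visit dates, with a statement that the comparison is not causal. Before doing so, reconcile Section 2.7 (T2 precedes rehabilitation) with Section 2.9 (physiotherapy throughout the study period).

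Items 1 to 3 are wording only and change no endpoint, visit or test. Item 4 uses data already collected. The cost is that the article's claims become more modest.

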## Introduction

1

Soft Tissue Sarcomas (STSs) are rare malignant tumors that account for 1% of adult solid cancers Gamboa et al. (1). Their annual incidence is estimated at approximately 24000 and 13500 new diagnoses in the European Union and the United States of America, respectively Gamboa et al. (1) Stiller et al. (2).

The clinical management of STSs is hindered not only by their rarity, but also by their biological diversity. Indeed, the World Health Organization recognizes more than one hundred histological and molecular variants, each displaying distinct pathological and clinical traits Jo and Fletcher (3). In addition, the STSs could develop in virtually any anatomical site, with the majority occurring in the limbs (60%), where the lower extremities are affected about three times more often than the upper ones Borghi and Gronchi (4), followed by the trunk (19%), retroperitoneum (15%) and head and neck (9%) Cormier and Pollock (5) Ebrahimpour et al. (6).

Although the STSs treatment generally considers both patient-related factors (e.g., age and comorbidities) and tumor-specific elements (e.g., histology, dimension and anatomical site), the combination of surgical excision and adjuvant therapies such as radiotherapy Haas et al. (7) or chemotherapy Maruzzo et al. (8) remains the reference standard Chowdhury et al. (9). The recommended radical resection requires excision of the tumor along with a margin of surrounding healthy tissue Casali et al. (10) creating large soft tissue defects which require additional reconstructive plastic surgery treatments Brunetti et al. (11).

Although effective from a reconstructive perspective, these operations compromise lower limbs sensorimotor functions inducing structural impairments (e.g., reduced joint movement, gait abnormalities), activity and social restrictions, and finally a reduction of Quality of Life (QoL) Gerrand and Furtado (12). Nonetheless, no studies have been conducted in this direction Andrews et al. (13).

Therefore, this study aims to deeply evaluate and objectively quantify the effects of a personalized rehabilitation protocol following STSs surgical treatment on clinical characteristics, sensorimotor performance, and QoL.

The paper is organized as follows: Section II describes the details of the experimental study, while Section III discusses the proposed clinical trial. The conclusions and future steps are exposed in Section IV.

## Materials and methods

2

### Study objectives

2.1

The main purpose of the study is to assess the effects of a personalized rehabilitation protocol on clinical status, motor performance, and quality of life in patients undergoing surgery for STS lower limbs.

To meet this objective, the following steps were planned:

Identification of clinical characteristics and motor damage after STS surgical removal;Impact of perioperative treatments and surgery on patients QoL;Impact of personalized post-operative rehabilitation treatment on patients clinical characteristics, motor performance and QoL.

### Study design and setting

2.2

The clinical investigation was designed as a prospective, observational, multicenter, uncontrolled study conducted on patients with STS localized in the trunk or in the lower limbs. It was approved by the Ethics Committee of the Fondazione Policlinico Universitario Campus Bio-Medico (Protocol number PAR 77.22 OSS), by the Ethics Committee Lazio 1 (Protocol number 420/CE Lazio 1) and registered on ClinicalTrials.gov (ID NCT06282237).

The study will be conducted at two centers: the Fondazione Policlinico Universitario Campus Bio-Medico as study sponsor, recruitment and surgery center, and the Centro Santa Maria della Provvidenza of the Fondazione Don Carlo Gnocchi in Rome as rehabilitation center.

The study is presented following the Standard Protocol Items: Recommendations for Interventional Trials (SPIRIT) Chan et al. (14) reported in **Figure 1**.

**Figure 1 f1:**
[figure not shown]
Standard Protocol Items: Recommendations for Interventional Trials (SPIRIT) schedule of enrollment, interventions and assessments. *T_0_* (within 7 days before surgery): baseline assessment; *T_1_* (within 7 days post-surgery): post-surgery assessment; *T_2_* (within 30 days post-surgery): pre-rehabilitation assessment; *T_3_* (within 90 days post-surgery): post-rehabilitation assessment.

### Study population

2.3

The patients’ screening will be carried out by a multidisciplinary team aiming to define the eligibility according to the following inclusion/exclusion criteria:

#### Inclusion criteria

2.3.1

*i)* Age over 18 years; *ii)* i) patients affected by primary STS localized in the lower limb, in the trunk where a wide excision is needed or in the retroperitoneum whose resection or injury may impair lower-limb function such as the iliopsoas muscle, the lumbar plexus roots or the femoral nerve with curative intent; *iii)* defects with a diameter ranging from 10 cm to 15 cm.

#### Exclusion criteria

2.3.2

*i)* Recurrent tumors; *ii)* metastatic diseases; *iii)* palliative surgery; *iv)* amputations.

### Recruitment

2.4

The study will be proposed to the patients attending the specialist general surgery department for STS of the Fondazione Policlinico Universitario Campus Bio-Medico.

Before the recruitment, the patients will be screened to evaluate the fulfilment of the study’s inclusion/exclusion criteria. Once eligibility is confirmed, the principal investigator or designated representatives will obtain written informed consent. This procedure will be conducted only after patients have received clear and comprehensive information regarding the study objectives, methodology, assessments, potential benefits and any eventual risks. The consent form will specify the procedures for pseudonymizing collected data, ensuring patients’ confidentiality. During this process, the principal investigator or designated representatives will be available to address questions and provide clarifications, thereby ensuring that patients will have a full understanding of the study.

In addition, the recruitment center will keep a detailed screening log recording all patients evaluated for participation and documenting whether they were subsequently included or not.

### Sample size

2.5

Based on the annual incidence of STS cases managed at the surgical center, a total of 50 patients will be recruited. Given the current absence of evidence regarding personalized rehabilitation in this population, the obtained results will be exploratory and will serve as a basis for determining the appropriate sample size in similar future trials.

### Baseline assessment

2.6

Once the written informed consent is acquired, a baseline assessment will be conducted for each patient. Concerning patient’s demographic and clinical characteristics, the following data will be collected.

Demographics (e.g., age, gender, height, mass);Past medical history;Tumor site;Histopathological tumor characteristics;Tumor staging;Information on adjuvant and/or neoadjuvant therapies and surgery;Medications taken;Functional impairments evaluated through the Musculoskeletal Tumor Society Rating Scale differentiated for the Lower Limb (MSTS-LL) Enneking et al. (15). This scale includes six domains regarding pain, functions, emotional acceptance, use of an external aid, walking, and lifting capabilities: it provides a total score ranging from 0% to 100% with higher values indicating better functional status;Activity limitations evaluated through the Toronto Extremity Salvage Score differentiated for the Lower Limb (TESS-LL) Davis et al. (16). It contains 30 questions assessing how difficult daily activities are (e.g., mobility, working, and wearing) execution on a scale from 0 (i.e., impossible to perform) to 5 (i.e., no difficulty). The final score ranges from 0% to 100% with higher values indicating better function;Pain evaluated through the Numerical Rating Scale (NRS) Downie et al. (17) and the Brief Pain Inventory (BPI) Cleeland and Ryan (18). The former quantifies pain in adult with a score ranging from 0 (no pain) to 10 (worst pain imaginable), the latter assesses pain intensity and its interference with daily activities with a score ranging from 0 to 10 with higher values indicating more severe pain and greater functional impairment. In addition, the neuropathic pain will be evaluated through the Douleur Neuropathique en 4 Questions (DN4) Bouhassira et al. (19) and the Leeds Assessment of Neuropathic Symptoms and Signs (LANSS) Bennett (20). The former includes 10 items: seven are related to patient-reported symptoms (i.e., burning, painful cold, electric shocks, tingling, needles, numbness, and itching) and three to clinical examination (i.e., hypoesthesia to touch, hypoesthesia to pinprick and pain provoked by brushing). Each positive answer scores 1 point, with a total score ranging from 0 to 10: a score of 4 or higher is indicative of neuropathic pain. The latter allows the discrimination between the nociceptive pain and the neuropathic one, combining subjective questions regarding symptoms (e.g., burning sensations, tingling, electric shocks) and objective sensory tests (e.g., changes in sensitivity to touch or pinprick). It provides a total score ranging from 0 and 24 with a value greater than 12 indicating a significant neuropathic component to the pain. From a general perspective, the use of the NRS, BPI, DN4 and LANSS will allow a granular characterization of the patient’s pain, including intensity, impact on activities and qualitative sensory descriptors;The perceived QoL evaluated through the Short Form Health Survey 36 (SF-36) Ware Jr (21) and the European Organisation for Research and Treatment of Cancer Quality-of-Life Questionnaire (EORTC QLQ-C30) Aaronson et al. (22). The former comprises 36 items evaluating eight health domains QoL (i.e., physical functioning, role functioning, bodily pain, general health, vitality, social functioning, role emotional and mental health) with a score ranging from 0 to 100 with higher values indicating a better QoL. The latter focuses on five functional domains (i.e., physical, role, emotional, cognitive, and social), QoL and eight symptom-related dimensions (i.e., fatigue, nausea and vomiting, pain, dyspnea, insomnia, loss of appetite, constipation, diarrhea, and financial difficulties) with each item scored on a scale from 0 to 100. Higher values in the functional domains and QoL indicate better well-being, whereas higher values in the symptom scales reflect a greater symptom burden.
